**Fig. 2 Fig2:**
[figure not shown]
High-resolution electroanatomical voltage mapping (left) showing a re-entry circuit of approx. 3.6 × 1.5 cm in the cardiac septum (red circle) and corresponding axial plane in the radiation treatment planning system (right) showing the target lesion in the septum (orange circle) and the planning target volume which included a 5 mm uncertainty margin (red circle)

Radiosurgery will be performed as described previously [22–24] as single fraction treatment with a dose of 25 Gy prescribed to the 95% PTV-encompassing isodose line (PTV D95% ≥ 25 Gy). There is currently no evidence from any human or preclinical studies that may point at the possible benefits of dose reduction [34] or increase [22–25], though future clinical trials may explore the possibility to reduce the full target dose or the dose to parts of the target for selected patients. Contrary to the previous studies and supported by preclinical studies [34], we allow higher maximum doses within the TV. The near-maximum dose is limited to 32.5 Gy (PTV D2% ≤ 32.5 Gy), with dose peaks exceeding 30 Gy being desirable, though exclusively centered in the TV (TV *D*_max_ ≥ 30 Gy and PTV − TV *D*_max_ ≤ 30 Gy). Dose-limiting constraints to nearby critical structures are well described in the literature [19, 22–26, 32, 34, 43–45, 50, 71], yet dose limits from radiosurgery to compartments in the heart and heart substructures such as valves or papillary muscles are largely unknown and have only been recently reported though not yet correlated to toxicity [23]. Dose limits for the RAVENTA trial are presented in Table 1. One minor, but no major violation to the dose limits is allowed for the RAVENTA trial. This may result in the exclusion of patients from the trial after treatment planning (e.g., if the PTV is close or overlapping with coronary arteries or the stomach).

**Table 1 Tab1:** Organs at risk dose recommendations and dose limitations

Organs at risk	Dose recommendations/dose limitations
Aorta	Dose limitations: *D*_max_ ≤ 20.0 Gy Minor protocol deviation: 20 Gy < *D*_max_ ≤ 25 Gy Major protocol violation: *D*_max_ > 25 Gy
Left coronary arteries	Dose limitations: *D*_max_ ≤ 14.0 Gy Minor protocol deviation: 14 Gy < *D*_max_ ≤ 20 Gy Major protocol violation: *D*_max_ > 20 Gy
Superior vena cava	Dose recommendations: *D*_50%_ ≤ 0.6 Gy
Left atrium	Dose recommendations: *D*_max_ ≤ 4.4 Gy
Whole heart minus PTV	Dose recommendations: *D*_50%_ ≤ 5 Gy
Esophagus	Dose limitations: *D*_max_ ≤ 14.5 Gy and *V*_9Gy_ ≤ 1 ccm Minor protocol deviation: *D*_max_ ≤ 19 Gy, *D*_1ccm_ ≤ 14.5 Gy and *V*_9 Gy_ ≤ 4 ccm Major protocol violation: *D*_max_ > 19 Gy || *D*_1ccm_ > 14.5 Gy || *V*_9 Gy_ > 4 ccm
Trachea	Dose limitations: *D*_max_ ≤ 15 Gy and *V*_10 Gy_ ≤ 1 ccm Minor protocol deviation: *D*_max_ ≤ 20 Gy, *D*_1 ccm_ ≤ 15 Gy and *V*_10 Gy_ ≤ 4 ccm Major protocol violation: *D*_max_ > 20 Gy || *D*_1 ccm_ > 15 Gy || *V*_9 Gy_ > 4 ccm
Bronchial tree	Dose limitations: *D*_max_ ≤ 15 Gy and *V*_10Gy_ ≤ 1 ccm Minor protocol deviation: *D*_max_ ≤ 20 Gy, *D*_1 ccm_ ≤ 15 Gy and *V*_10 Gy_ ≤ 4 ccm Major protocol violation: *D*_max_ > 20 Gy || *D*_1 ccm_ > 15 Gy || *V*_9 Gy_ > 4 ccm
Spinal canal	Dose limitations: *D*_max_ ≤ 7 Gy and *V*_6 Gy_ ≤ 0.1 ccm Minor protocol deviation: *D*_max_ ≤ 8 Gy, *V*_6 Gy_ ≤ 1 ccm Major protocol violation: *D*_max_ > 8 Gy || *V*_6 Gy_ > 1 ccm
Skin	Dose limitations: *D*_max_ ≤ 14.4 Gy and *V*_10 Gy_ ≤ 10 ccm Minor protocol deviation: *D*_max_ ≤ 16 Gy, *V*_14.4 Gy_ ≤ 10 ccm Major protocol violation: *D*_max_ > 16 Gy || *V*_14.4 Gy_ > 10 ccm
Whole lungs	Dose limitations: *V*_100% _− *V*_7Gy_ ≥ 1500 ccm (*V*_7 Gy_ remaining volume > 1500 ccm) and *D*_5%_ ≤ 20 Gy and *D*_50%_ ≤ 3.5 Gy Minor protocol deviation: *V*_100% _− *V*_7Gy_ ≥ 1000 ccm (*V*_7 Gy_ remaining volume > 1000 ccm), *D*_6.5%_ ≤ 20 Gy and *D*_50%_ ≤ 5 Gy Major protocol violation: *V*_100% _− *V*_7 Gy_ < 1000 ccm (V_7 Gy_ remaining volume < 1000 ccm), *D*_6.5%_ > 20 Gy and *D*_50%_ > 5 Gy
ICD (major electronics)	Dose limitations: *D*_max_ ≤ 0.5 Gy and blocked from primary beam irradiation Minor protocol deviation: 0.5 Gy < *D*_max_ ≤ 1.0 Gy Major protocol violation: *D*_max_ > 1.0 Gy

All SBRT techniques/platforms available at the meantime are well capable to generate highly conformal treatment plans anywhere in the body [42, 66, 67], though we are restricting the use of higher energies (maximum 6 mega electronvolt) for cardiac radiosurgery due to the presence of an ICD in these patients [72, 73]. Plan optimization will be performed using the best-practice guidelines for each system according to the ALARA (as low as reasonably achievable) principle for critical structures inside and outside of the heart. Due to radiation biology considerations, a treatment (beam-on) time of less than 20 min is desirable (e.g., using volumetrically modulated treatment techniques and flattening filter-free beams) to minimize the influence of cell-repair mechanisms under prolonged irradiation [74]. The actual treatment will be performed under close cardiological monitoring (continuous ECG monitoring and standby cardiac emergency team during treatment) according to the guidelines of the DGK (German Society of Cardiology) and DEGRO (German Society of Radiation Oncology) [72]. Patient repositioning and target localization will be performed by means of integrated image guidance ideally using a time-resolved or triggered volumetric cone-beam CT (CBCT) according to the motion management strategy. Alternatively, stereoscopic X-ray images may be used for image guidance insofar as landmarks near the target (e.g., ICD leads) can be precisely located and used for motion compensation. Directly after treatment the ICD system will be evaluated for functionality and will be reprogrammed, if necessary. Follow-up of the patients consisting of clinical evaluation, ICD checks and Holter monitor readout, transthoracic echocardiography and electrocardiography will be performed in the first 5 days daily after treatment, with hospital discharge ideally in this time, and 15 and 31 days, 6 and 8 weeks, and 4, 5, 6, 9, and 12 months after cardiac radiosurgery. Additionally, a thoracic CT will be performed at 3 months after treatment to assess possible asymptomatic radiation pneumonitis and pericarditis.

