### Ethical and legal considerations, quality harmonization, and patient safety

As RA/CRS is deemed an experimental therapy for VT, the RAVENTA trial needed authority approval which has been obtained from the German National Radiation Protection Authority (Bundesamt für Strahlenschutz, BfS, reference number Z5-22463/2-2018-054) and from the leading ethics committee of the University of Kiel (reference number 555-18), and subsequently by the ethics committees responsible for further participating centers. The clinical trial registration number at clinicaltrials.gov is NCT03867747. The study is monitored and audited by the center for clinical trials (ZKS Luebeck, Germany, protocol number ZKS-121-09). Sponsor of the study is the University Medical Center Schleswig Holstein (UKSH).

With respect to clinical trial harmonization for this experimental therapy, the evaluation criteria and examination protocols, as well as materials such as test sheets are uniform for all centers. Furthermore, the documentation for commissioning, dose calibration, and quality assurance of the respective radiosurgery treatment system are centrally reviewed in accordance with the national standards and laws. An independent absolute dose audit for each treatment system is mandatory every 2 years. A benchmark study consisting of target volume definition and treatment planning for exemplary VT RA/CRS cases is ongoing, though the initial results were already discussed. In brief, general consensus was reached between the centers; however, it was decided to perform a planning target volume and treatment plan joined group interdisciplinary review within the participating centers for all patients before treatment to quickly harmonize and improve as a whole group.

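### Table 1 dose-limit classes: the lung row's 'and' leaves most serious breaches unclassified, and the trachea and bronchial rows switch from V10Gy to V9Gy in the major class

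*Protocol article*

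**What the plan says.** The protocol article, Study treatment, sets the rule "One minor, but no major violation to the dose limits is allowed for the RAVENTA trial". On its consequence it says: "This may result in the exclusion of patients from the trial after treatment planning". The classes are defined in Table 1.

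- **Whole lungs.** The minor class needs three bounds to hold together: at least 1000 ccm of lung below 7 Gy, and "D*_6.5%_ ≤ 20 Gy and *D*_50%_ ≤ 5 Gy". The major class reverses each sign but keeps the conjunction: less than 1000 ccm below 7 Gy, and "D*_6.5%_ > 20 Gy and *D*_50%_ > 5 Gy".
- **Trachea and bronchial tree.** The minor class, besides a Dmax bound of 20 Gy, requires "D*_1 ccm_ ≤ 15 Gy and *V*_10 Gy_ ≤ 4 ccm". The limit class also uses V10Gy (at most 1 ccm). The major class, after Dmax > 20 Gy, reads "D*_1 ccm_ > 15 Gy || *V*_9 Gy_ > 4 ccm".
- **Esophagus, for comparison.** The major class, after Dmax > 19 Gy, reads "D*_1ccm_ > 14.5 Gy || *V*_9 Gy_ > 4 ccm". This row uses V9Gy in all three classes.

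The spinal canal and skin rows also join their major criteria with `||`.

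**The concern.** If a minor deviation requires every relaxed bound to be met, a major violation should be the failure of any one of them. The lung row instead asks for all of them to fail. A plan that breaks one or two bounds is then neither minor nor major: it does not earn the single minor exception, but nothing expressly labels it as barred. This is the safety-relevant error. The primary endpoint and the five-patient interim look cover only 30 days, while the thoracic CT for asymptomatic pneumonitis comes at 3 months, so the planning gate is an important advance protection for the lungs.

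The airway rows err the other way. The volume receiving at least 9 Gy is never smaller than the volume receiving at least 10 Gy. A plan can therefore satisfy the limit or minor class on V10Gy and still be major on V9Gy. A patient with few other options could be excluded although the plan meets the table's own limit.

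**Working it through.** The plan gives no figure to reproduce. The check is one of logic on the Table 1 thresholds. Lung volumes and example plans below are assumptions.

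**1. Lung row, all breach patterns.** Let R = lung volume below 7 Gy. The three possible breaches are R < 1000 ccm, D6.5% > 20 Gy and D50% > 5 Gy, giving 2³ = 8 patterns.

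| Breaches | Patterns | Class as printed | Class if joined by 'or' |
|---|---|---|---|
| none | 1 | limit or minor | limit or minor |
| exactly one | 3 | none | major |
| exactly two | 3 | none | major |
| all three | 1 | major | major |

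So 6 of 8 patterns are unclassified as printed. With 'or', 7 are major and none is unclassified.

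**2. The six patterns can all occur.** Example plans:

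| Lung (ccm) | Share above 20 Gy | Share above 7 Gy | R (ccm) | D50% (Gy) | Breached |
|---|---|---|---|---|---|
| 1500 | 5% | 40% | 900 | 4 | R |
| 4000 | 8% | 20% | 3200 | 3 | D6.5% |
| 4000 | 5% | 45% | 2200 | 6 | D50% |
| 1500 | 8% | 40% | 900 | 4 | R, D6.5% |
| 1500 | 5% | 45% | 825 | 6 | R, D50% |
| 4000 | 8% | 45% | 2200 | 6 | D6.5%, D50% |

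Here R = lung volume × (1 − share above 7 Gy), and D6.5% exceeds 20 Gy when more than 6.5% of the lung does.

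**3. How far the gap reaches.** If D50% < 7 Gy, less than half the lung volume V receives 7 Gy, so R > V/2. When V ≥ 2000 ccm, R > 1000 ccm, the first term fails and the conjunction is false. Such a plan is never major, whatever its D6.5%. D50% can thus run from above 5 Gy to just under 7 Gy, which is 7/3.5 = 2 times the limit, without the label.

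The printed major class also needs V7Gy > V − 1000:

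- V = 3000 ccm: 2000/3000 = 67% of the lung at 7 Gy or more
- V = 4000 ccm: 3000/4000 = 75%
- V = 5000 ccm: 4000/5000 = 80%

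**4. Airway rows.** Two example plans:

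| Dmax (Gy) | D1ccm (Gy) | V10Gy (ccm) | V9Gy (ccm) | Limit or minor class | Major as printed (V9Gy > 4) | Major with V10Gy > 4 |
|---|---|---|---|---|---|---|
| 18 | 14 | 3 | 5 | minor | yes | no |
| 14 | 9.9 | 0.9 | 4.5 | within limit | yes | no |

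A grid of plausible values showed overlaps like these but no unclassified plans. Replacing V9Gy by V10Gy in the major class removes the overlap.

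**The case against.** The best counter-argument is that the lung row lacks a label, not a prohibition. Read as a whole, the rule tolerates one kind of departure from the limits, a single minor one. A plan with D50% of 6 Gy is beyond the limit and not minor, so nothing in the article allows it. The entry might also be read as a list of three thresholds, with the intended logic visible from the other rows.

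The airway error can only bar more plans, and where classes overlap the ban on major violations decides. The second airway example needs 4.5 − 0.9 = 3.6 ccm of airway between 9 and 10 Gy, and a marginal plan could be re-optimised before anyone is excluded. Finally, the section on ethical and legal considerations and quality harmonization commits the centers to "perform a planning target volume and treatment plan joined group interdisciplinary review within the participating centers for all patients before treatment", so a slip of this kind may well be noticed.

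Much of this stands as a limit on consequence. No sentence expressly permits an unclassified lung plan, the airway window is narrow, and the joint review lowers the risk that centers decide differently. It does not make the table right. The list reading sits badly with a table that uses `||` in all five other rows with several major criteria, and the reviewers have no corrected criterion to apply. Counting 6 of 8 patterns describes the logic, not the frequency of such plans.

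**Conclusion.** The concern holds on the text as printed and should be fixed. The lung major class is too permissive: it leaves 6 of 8 breach patterns without a class and, for lungs of 2000 ccm or more, cannot label any plan with D50% below 7 Gy as major. The trachea and bronchial major classes are too strict, in a narrow window where V9Gy exceeds 4 ccm but V10Gy does not.

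The lung 'and' is probably a slip for 'or', and the 9 Gy term was probably carried over from the esophagus row. Both are inferences. The 67%, 75% and 80% figures rest on assumed lung volumes; the 2000 ccm bound follows from the thresholds alone. The number of patients affected cannot be estimated from the article, and the operative protocol may be correct. Sample size, the interim rule and the primary test are untouched.

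**What to change.** Correct Table 1:

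- **Whole lungs, major:** remaining volume below 7 Gy < 1000 ccm `||` D6.5% > 20 Gy `||` D50% > 5 Gy.
- **Trachea and bronchial tree, major:** use one dose level across each row. V10Gy > 4 ccm matches the limit and minor classes; the radiation oncology and physics leads should confirm that 10 Gy is the intended level.
- **Optional, for clarity:** define minor as limit exceeded but within the minor bounds. The esophagus, trachea, bronchial tree, spinal canal, skin and lung rows give no lower bound for minor, unlike the aorta, left coronary and ICD rows. This is a matter of notation.

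The cost is a table correction. If the operative protocol carries the same text, plans already approved should also be rechecked against the corrected classes. No additional procedures or patients are needed.

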### Study objectives

The main objective of the RAVENTA trial is to evaluate safety of RA/CRS for VT. The primary endpoint is to assess the 30-day post-intervention safety defined as presence of both, complete radiosurgery delivery of the planned dose to the intended target area, and no possibly treatment-related serious adverse events (grade ≥ 3) in the first 30 days after treatment. This primary endpoint was chosen to ensure the early study termination which should be any major concern in the immediate time after radiosurgery arise. Based on the previous clinical data [19, 20, 22–31] for this endpoint, we assume that RA/CRS is feasible and safe in at least 70% (study stopping rule) and ideally in ≥ 95% of the treated patients.

Secondary study endpoints that will be evaluated within the first year of follow-up are:reductions in ventricular tachycardia episodes and ICD interventions,reductions in antiarrhythmic medication due to treatment effects,occurrence of possibly treatment-related adverse events,changes in patient-reported quality of life, andoverall survival.

Episodes of VT and ICD interventions will be assessed through Holter monitor readout. A blanking period of 6 weeks after treatment for the radiation effects to set in will be set forth and antiarrhythmic medication will be subsequently reduced if indicated by the reductions of VT episodes and ICD interventions. Adverse events will be assessed according to the Common Terminology Criteria for Adverse Events (CTCAE, version 5.0) and classified based on causality to RA/CRS with the categories: (a) no causal relationship, (b) unlikely causal relationship, (c) possible causal relationship, and (d) likely or definitive causal relationship. It will be of specific importance to distinguish between progression of the underlying heart disease and treatment-related adverse events. In unclear cases that are not ascribable to any of both, an adverse event will be assumed. These classifications are similar to the first larger clinical trial which already published detailed results [22]. Quality of life will be recorded through the EQ-5D-5L questionnaire and overall survival will be captured as any patient contact. Due to the limited data, patients will also be followed after study completion of each patient and of the study to obtain further long-term safety data.

### Statistical planning

Based on Simon and Fleming's two-stage designs, an interim analysis is performed after the first 5 included patients have been assessed for the primary endpoint. Accordingly, the inclusion of additional patients cannot be carried out until at least 30 days after the completion of treatment of the fifth patient. The sample size planning is based on 95% success for the primary endpoint (i.e., less than or equal to 5% possibly related serious adverse events within 30 days after delivery of the full planned dose), significance level of 5% and a power of 90%.

In a two-stage test procedure with multiple significance level of nominal 0.05 and a power of nominal 0.90 after observing 5 and possibly 20 cases, safety is tested. An insufficient safety of 70% (null hypothesis H0) should quickly and safely lead to the rejection of the hypothesis of a safety of 95% (H1), but with a probability of stopping for futility below 0.5. However, if the safety is 95%, then this should ultimately lead to the rejection of the null hypothesis of insufficient safety. If the safety is in between, the statement is confined to the confidence interval. Thus, the expected number of patients assuming H0 is 12.9, because with a probability of 0.47, the study will terminate after 5 patients, and if H1 is true, it is 19.7 patients. This design differs from the Simon two-stage design in that it does not minimize the expected number of patients, but does the interim analysis for the smallest possible number of cases. Calculations used R package gsDesign, function gsBinomialExact. Loss to follow-up is part of the primary endpoint.

The analysis strategy is the composite strategy of ICH E9 (R1) Addendum on Estimands, i.e., loss to follow-up, and intercurrent events like rescue LVAS will be counted as a lack of both, safety and feasibility. Toxicity is summarized in a graph as cumulative frequencies of the toxicity levels for each time point. Mortality is presented as a Kaplan–Meier curve. Effectiveness is described by measures of location and scatter (95% confidence intervals) of the distributions of the features and differences to baseline. In general, those will be confidence intervals derived from the score function for proportions and Hodges–Lehmann intervals for medians. The dimensions of quality of life are represented as trajectories; supplemented by a median trajectory, with missing values being imputed by the worst value in the same patient. For the quality-of-life index determined according to the published weights, averages and distributions are given for the individual times and for the areas under the curves. Adverse events are tabulated by organ system, intensity, and relatedness.

### Trial duration and study termination

The patient accrual is estimated to be completed within 2 years after start (estimated start in November 2019), with a follow-up period of 1 year after the inclusion of the last patient. The clinical trial should be concluded 3 years after first inclusion. Early termination of the trial will occur if the toxicity of the performed RA/CRS is determined to be unacceptable for any possibly related serious adverse events during the study (i.e., adverse events ≥ grade 3 in the first month after treatment in more than one of the first five or more than two out of ten patients). The study can be terminated early, if (a) the hypothesis of the study can be answered by new data, or (b) events observed later after treatment are more frequent than must be expected given published data, or (c) the recruiting target is not met during the recruitment phase.

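### The stated expected sample size (12.9) and early-stopping limit (below 0.5) leave out the mandatory ten-patient termination rule

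*Protocol article*

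**What the plan says.** **Statistical planning.** Safety is tested with a "multiple significance level of nominal 0.05 and a power of nominal 0.90 after observing 5 and possibly 20 cases". The null value is introduced as "An insufficient safety of 70% (null hypothesis H0"; the alternative is 95%. A low true safety should end the trial quickly, "but with a probability of stopping for futility below 0.5". The result is given as: "the expected number of patients assuming H0 is 12.9, because with a probability of 0.47, the study will terminate after 5 patients". Under the alternative the expected number is 19.7. The interim at five patients is on the primary endpoint. Under the composite strategy described there, loss to follow-up and intercurrent events such as rescue LVAS also count as failures.

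**Trial duration and study termination.** Early termination is to follow if possibly related events of grade 3 or higher arise in the first month "in more than one of the first five or more than two out of ten patients". This clause is mandatory; the other grounds listed after it are permissive.

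**Study objectives.** Success is complete delivery of the planned dose together with no possibly related serious adverse event (grade 3 or higher) within 30 days. The treatment is assumed to be one that "is feasible and safe in at least 70% (study stopping rule", as the text puts it.

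**Ethical and legal considerations, quality harmonization, and patient safety.** The interim analysis after five patients and the termination rules are both listed among several safety layers.

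**The concern.** Two things do not line up.

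- **Number of looks.** The calculation has one interim, at five. The termination section adds a binding stopping point at ten. The printed expected sample size, and the limit of 0.5 on early stopping, belong to a trial without that second point.
- **What is counted.** The interim uses the composite primary endpoint: incomplete delivery, related grade 3 or higher events, loss to follow-up and intercurrent events. The termination rule counts related grade 3 or higher events only. It is also the only place where a stopping rule is written in counts of patients. Nothing says how the two combine.

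Safety is the primary endpoint, and early stopping is one of the trial's main safeguards. The monitoring board, the authorities and the sponsor need one unambiguous rule and operating figures that describe it.

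**Working it through.** **Inputs.** Failure probability p = 0.30 under H0 and 0.05 under H1; looks at 5 and 20 (Statistical planning). Termination at two or more of the first five, or three or more of ten (Trial duration and study termination). I take ten to mean the first ten patients, assessed together once ten have been observed.

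**1. Reproducing the stated figures (looks at 5 and 20).** The stop at five is at two or more failures:

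- H0: P(stop at 5) = 1 − 0.7⁵ − 5 × 0.3 × 0.7⁴ = 1 − 0.1681 − 0.3602 = 0.4718 (stated 0.47). Expected N = 20 − 15 × 0.4718 = 12.92 (stated 12.9).
- H1: P(stop at 5) = 0.0226. Expected N = 20 − 15 × 0.0226 = 19.66 (stated 19.7).

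A cut-off of one failure would give 0.832 under H0, and three would give 0.163. So the calculated design stops at two or more of five, and it has no look at ten.

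**2. Adding the ten-patient rule, every failure being a related grade 3 or higher event.** The trial stops at ten if it passed the first look with 0 or 1 failures and then reaches a cumulative three:

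- P(stop at 10) = P(0 of 5) × P(≥3 of 5) + P(1 of 5) × P(≥2 of 5) = 0.1681 × 0.1631 + 0.3602 × 0.4718 = 0.0274 + 0.1699 = 0.1973.
- Total early stopping under H0 = 0.4718 + 0.1973 = 0.669.
- Expected N under H0 = 5 × 0.4718 + 10 × 0.1973 + 20 × 0.3309 = 10.95.
- Under H1: total early stopping 0.028, expected N 19.61.

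**3. Adding it when only a share s of failures are such events (assumption; no split is given).** The interim at five still counts all failures. At ten, only events count, each with probability e = 0.30s per patient. Among trials that pass the first look:

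- P(no event so far) = 0.1681 + 0.3602 × (1 − s)
- P(one event so far) = 0.3602 × s
- P(stop at 10) = P(no event so far) × P(Bin(5, e) ≥ 3) + P(one event so far) × P(Bin(5, e) ≥ 2)

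For s = 1/2, e = 0.15: 0.3481 × 0.0266 + 0.1801 × 0.1648 = 0.0389.

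| Share of failures that are related grade ≥3 events | P(stop at 5) | P(stop at 10) | Total early stop, H0 | Expected N, H0 |
|---|---|---|---|---|
| Stated design, no look at ten | 0.472 | – | 0.472 | 12.92 |
| 1/3 | 0.472 | 0.013 | 0.485 | 12.79 |
| 1/2 | 0.472 | 0.039 | 0.511 | 12.53 |
| 2/3 | 0.472 | 0.080 | 0.552 | 12.13 |
| All | 0.472 | 0.197 | 0.669 | 10.95 |

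Under H1, expected N lies between 19.61 and 19.66 in every case.

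**4. Type I error and power.** The article prints no final cut-off. At 18 or more successes in 20, the two-look design gives a type I error of 0.034 and power of 0.915, in line with the nominal 0.05 and 0.90. At 17 the type I error would be 0.096; at 19 the power would be 0.736. So 18 is the inferred value. Three events in the first ten already make 18 of 20 impossible, so the ten-patient stop leaves both figures unchanged.

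**The case against.** The best defence is that the two sections are separate layers. One is an efficacy-style interim on the composite endpoint; the other is a narrower toxicity rule. The patient-safety section lists both, and either could stop the trial. Much of this stands, and it rules out several stronger readings.

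- **That 0.47 is wrong.** It is stated as the probability of ending after five patients, and for the primary-endpoint interim it is correct whatever the mix of failures.
- **That the two rules contradict each other in the first five.** A reader might infer that one related event plus one loss to follow-up stops the trial under one section and lets it continue under the other. The termination section gives grounds for stopping; it does not say when the trial goes on.
- **That early protection is weaker than stated.** Counting events only, stopping at five would have probability 0.165 if half of the failures are events. That requires the termination rule to replace the primary-endpoint interim, which the text keeps.
- **That the 70% described as a stopping rule in Study objectives conflicts with stopping at 7 of 10.** It is plausibly just a label for the null value.
- **That the limit of 0.5 is certainly broken.** The limit is worded for futility in a two-stage test and may be meant for the first look only. The total also stays below 0.5 if one third of failures are events.

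The defence does not remove the main point. A mandatory second rule changes the expected sample size and the total chance of stopping early even if it is a separate layer, and no figure in the article includes it. The article does not say that the layers are independent or how they combine. The safety flowchart (Fig. 3) and the full protocol are not shown and may clarify this, but the article prints both the rule and the figures.

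**Conclusion.** The point holds in a limited form. The arithmetic in Statistical planning is right for looks at 5 and 20. It does not describe the design with the ten-patient termination rule.

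With that rule and the interim at five both in force, total early stopping at 70% safety rises from 0.472 to between 0.485 (one third of failures are related grade 3 or higher events) and 0.669 (all are). Expected N falls from 12.9 to between 12.79 and 10.95. The total exceeds 0.5 in the cases of one half, two thirds and all. The upper figures are the extreme case, not a central estimate. If the trial stops as soon as a limit is crossed, rather than at five or ten patients, expected N in that extreme case is 10.04.

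The effect under H1 is negligible, and the test itself is untouched on the inferred 18/20 cut-off. What needs repair is the stated early-stopping behaviour under H0, and the silence on how an event-only rule and a composite-endpoint rule work together.

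**What to change.** Reconcile Study objectives, Statistical planning, Trial duration and study termination, and the patient-safety section so that they state the same thing on three points:

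1. whether ten patients is a formal look;
2. which failures each look counts (composite primary endpoint, or related grade 3 or higher events only);
3. how the rules combine. If both are kept, say that either one triggers a stop.

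If the ten-patient rule stays, rerun the exact binomial calculation with it. Restate the total early-stopping probability and the expected N under H0 and H1, giving the assumed share of failures that are related events. Say whether the limit of 0.5 applies to the first look only or to all early stopping. In Study objectives, make clear whether 70% is the null value or a stopping criterion.

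Which stopping rule to keep is the sponsor's decision. The cost is protocol wording and one rerun of a short calculation; the sample size of 20 and the inferred final test need not change.
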